#### Primary outcome measure

The vision ability of infants at baseline (T0) and 12-month follow-up (T2) (primary outcome measure) will be determined with vision function assessments.

Visual acuity assessment: Teller Acuity Cards (half set, consisting of 8 cards) will be used in modulated gratings (between 0.23 and 26 cycles/cm) to measure maximum acuity. Testing distance of 38 cm is used for infants 0–6 months allowing for spatial frequencies measurement. This wide range is appropriate for visual acuity measurement in infants with low vision.

Infant Battery for Vision will be used.^35^ It consists of a set of standard assessments, testing:

Spontaneous visual behaviour.Fixation.Oculomotor movements (nystagmus, strabismus).Visual primary perception.Visual fields* using the confrontation method.Contrast sensitivity (Hiding Heidi cards).Visual adult-infant interaction (face recognition, response to facial expressions).

The detailed explanation regarding the performance of the visual function assessments is provided in the study-specific written manual and video recording examples formats.

Assessments of vision will also include:

Ophthalmological assessment, including eye examination, assessment of refractive error, eye deviation and oculomotor behaviour.Near detection scale (Sonsken)^36^: a 10-point scale ranging from no light awareness (0) to 0.1 cm ‘lure’ (9) according to visual fixation on diminishing size lures at standard to near distance (30 cm).The Preverbal Visual Assessment (PreViAs), a simple 30-item parent questionnaire, will be used for screening visual abilities (visual attention, visual communication, visual-motor coordination and visual processing).^37^ The PreViAs will be used for screening visual abilities (visual attention, visual communication, visual-motor coordination and visual processing).

#### Secondary outcome measures

The Peabody Developmental Motor Scales, Second Edition (PDMS-2)^38^ at T1, T2 is a standardised and normed scale for children aged from birth to 6 years and has been validated for use as a discriminative measure. Infant primary motor outcomes at 12 months CA will be assessed using the PDMS-2, a standardised, norm-referenced measure used to evaluate the gross and fine motor development of children aged birth to 6 years.

The Bayley Scales of Infant and Toddler Development, Third Edition (BSID-III)^39^ at T2, a standardised and norm-referenced assessment of cognitive, motor, language and social-emotional development of infants and toddlers 0–3 will be assessed using the gold standard Bayley Scales of Infant and Toddler Development, Third Edition. These assessments will be supplemented by parent report on the norm-referenced forms.

The COPM^40^ at T1, T2 is used to assist parents in setting and prioritising goals and measuring parent-perceived change of their infant’s performance of the goal and own satisfaction with progress. The semi-structured initial interview to establish the goals will focus on what aspects of the infant’s vision behaviour the parent wants or needs to see improved.

Pediatric Evaluation of Disability Inventory-Computer Assisted Test (PEDI-CAT)^41^ at T1, T2 is a parent-reported measure of their child’s independence in self-care, mobility and social function that has been analysed in both children with disabilities and those with typical development. Raw scores will be converted to standardised scores using normative data (0–100) to measure change in function. Developmental outcomes in self-care, mobility and social function will be assessed at 12 months CA using the PEDI-CAT, a standardised, norm-referenced assessment of independence in self-care. The instrument measures functional outcomes across four domains: daily activities, the ability to perform living skills; mobility, the ability to move around the home and in the community; and social/cognitive, the ability to participate and effectively engage in social situations. Responsibility, the fourth domain, will not be assessed in this study.^42^ The PEDI-CAT has good discriminant validity in CP populations, between children with and without disability, and demonstrates concurrent validity with the Wee-FIM (Functional Independence Measure for Children) in children with brain injury and developmental disabilities.^43^ The test is valid, reliable and responsive in this population, takes 10–15 min to complete and requires no formal training.

DASS-21^30^ at T1, T2 is a 21-item questionnaire that assesses symptoms of depression, anxiety and stress in the parent/caregiver.

Emotional Availability Scales (EAS) and Self Report^31^ at T1, T2 is based on a naturalistic observation of a parent-infant interaction in the family’s home to measure parental sensitivity, parental structuring, parental non-intrusiveness, parental non-hostility, child responsiveness and child involvement, and a global relationship quality rating. The video will be 15 min long. Parents will be asked to video the interaction, or telemedicine video recording will be used. The EAS will be assessed by an independent rater trained in scoring the EAS. The EAS self-report is a 32-item parent-report measure of emotional availability within the parent-child relationship.

The Infant Toddler Quality of Life Questionnaire (ITQOL)^44^ at T1, T2: ITQOL is a 103-item parent-reported questionnaire of quality of life for infants and toddlers aged 2 months to 5 years, and measures quality of life across physical, mental and social well-being. For each of the 10 concepts (physical functioning, growth and development, bodily pain, temperament and moods, general behaviour, getting along, general health perceptions, change in health, and parental impact: emotional/time/family activities/family cohesion), item responses are scored, summed and transformed to a scale from 0 (worst health) to 100 (best health).

Clinical Brain Structure and Neuroplasticity measures. When possible, brain MRI will be acquired on 1.5T or 3T scanners in the neonatal period (as part of recruitment) (T0) and at 12-month follow-up (T2). All attempts will be made to complete a natural sleep MRI with either (i) feed and wrap methods in the neonatal period and/or (ii) at 12 months CA the implementation of a desensitisation programme to familiarise the child to the scanner noises so that sleeping scans can be performed. In addition to the recommended clinical MRI, we will acquire high-resolution structural images and multi-shell high angular resolution diffusion-weighted images (high angular resolution diffusion imaging (HARDI) and neurite orientation density and dispersion imaging (NODDI)).^45^ These additional research sequences will take approximately 15 min and will be acquired at the same time as the recommended clinical scan. Families who do not wish for their child to have an MRI around 12 months CA can participate in the study without performing the brain MRI scan.

All assessment tools and instruments intended for use by clinical researchers in this study are available in English. Additionally, tools requiring parental completion, including the DASS-21, ITQOL and EAS-R, are available in each local language (English, Georgian and Italian) to ensure accessibility and accurate data collection across study sites.

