**Methods and analysis:**

A two-group RCT will be conducted. Infants at 3–6 months at entry, with severe visual impairment and at high risk of CP, will be enrolled and randomised (n=16 per group) to receive the VISIBLE intervention compared to SCC. Randomisation will be completed through an independent automated process (Research Electronic Data Capture). VISIBLE intervention will be delivered by a therapist through home visits (90–120 min) once every 2 weeks. Completion of 10 visits (80% of the intervention target dose) within 6 months is required for adherence to the VISIBLE trial. Outcome will be assessed at 12 months CA. Visual function will be evaluated with the Infant Battery for Vision, motor outcomes with the Peabody Developmental Motor Scales, Second Edition. Developmental quotients, infant quality of life, parent well-being and parent-infant relationship will be also monitored through standardised tools.

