### Data analysis plan

A multisite RedCap programme database will be used for this study. Study personnel at each site will enter the data onto RedCap, a secure web platform for the construction and management of surveys and online databases. All the data of the same patient will be collected under an ID number. Videos of sessions will be taken to ensure fidelity of intervention visits provided by the study therapists.

All measures will be undertaken to avoid missing data for the primary outcome. Rescheduling of appointments for assessments will be done if the data collection cannot be completed in one appointment. Should vital data be missing, use of all available data will be used, as recommended through methods such as multiple imputation and likelihood-based analysis.

Statistical analysis will be conducted using SPSS following standard methods for RCTs. Intention-to-treat analysis will be applied to minimise inflation of treatment effects, consistent with Consolidated Standards of Reporting Trials (CONSORT) guidelines.^46^ Descriptive statistics will be used to summarise baseline characteristics and outcome measures for both treatment groups, with continuous variables reported as means and SDs (if normally distributed) or medians and IQRs (if skewed), and categorical variables as frequencies and percentages. Normality of continuous data will be assessed using the Shapiro-Wilk test and visual inspection of histograms and quantile-quantile (Q-Q) plots. If data are normally distributed, intervention efficacy will be tested using general linear models, specifically Analysis of Covariance (ANCOVA), adjusting for baseline values. If substantial skewness is observed and not resolved through transformation, non-parametric alternatives such as the Mann-Whitney U test for between-group comparisons will be used. Appropriate adjustments for multiple comparisons will be applied where necessary.

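### PEDI-CAT change is to be measured on a norm-referenced score, which records standing against peers and can show no change or a decline in an infant who has gained function

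*Protocol article*

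**What the plan says.** Under Secondary outcome measures, the protocol article schedules the PEDI-CAT twice: it "at T1, T2 is a parent-reported measure of their child’s independence in self-care, mobility and social function". The next sentence fixes both the score and its purpose: "Raw scores will be converted to standardised scores using normative data (0–100) to measure change in function". The same paragraph calls the instrument "a standardised, norm-referenced assessment of independence in self-care", places the outcome at one nominal age ("Developmental outcomes in self-care, mobility and social function will be assessed at 12 months CA using the PEDI-CAT"), and adds that "The test is valid, reliable and responsive in this population", without saying which type of score that refers to.

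The abstract gives age and severity at entry: "Infants at 3–6 months at entry, with severe visual impairment and at high risk of CP, will be enrolled and randomised". T1 precedes the start of the intervention and T2 is the 12-month follow-up (Statistical methods). The second aim is to show larger improvements than standard care, including in developmental outcomes (Aims).

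The Data analysis plan tests efficacy between arms with general linear models, "specifically Analysis of Covariance (ANCOVA), adjusting for baseline values", or with the Mann-Whitney U test if skewness persists. The article gives no PEDI-CAT norm means, norm SDs, floor or expected score distribution.

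**The concern.** The score and the job given to it do not match. A norm-referenced score answers how far an infant stands from the reference group. It does not answer how much function the infant has gained. The two answers separate most when the norms move quickly, as they do from 3–6 months to 12 months corrected age, and in infants expected to develop more slowly than the reference group. This trial studies exactly that period and population.

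What is at stake is the reading of change. Outcome measures are to be summarised by group. A flat or falling mean normed PEDI-CAT score could be taken to mean that function did not improve, or regressed, when the infants had in fact gained skills. The article also says that the data will be used to design a powered trial if there is initial evidence of efficacy, so the choice of metric may carry forward.

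**Working it through.** The article states no figure to reproduce on this point. All norm and floor values below are assumptions.

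**1. What norming does to a gain.** Take a generic normed score S = 50 + 10 × (raw − μ)/σ, with μ and σ the norm mean and SD at the infant's age. For an infant who stays at a fraction r of the norm mean:

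- raw gain = r × (μ at 12 months − μ at entry), always positive while the norms rise;
- S = 50 − 10 × (1 − r) × μ/σ, so S moves only if μ/σ moves.

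S is flat if σ grows in proportion to μ, falls if σ grows more slowly, and would rise if σ grew faster.

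Assume μ = 4 × age in months, so 12, 24 and 48 at 3, 6 and 12 months, and r = 0.5.

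| Assumed σ | Entry age | Raw score | S at entry | S at 12 months |
|---|---|---|---|---|
| 0.3μ | 3 months | 6 to 24 (+18) | 50 − 10×6/3.6 = 33.3 | 50 − 10×24/14.4 = 33.3 |
| 0.3μ | 6 months | 12 to 24 (+12) | 50 − 10×12/7.2 = 33.3 | 33.3 |
| 0.25μ + 2 | 3 months | 6 to 24 (+18) | 50 − 10×6/5 = 38.0 | 50 − 10×24/14 = 32.9 |
| 0.25μ + 2 | 6 months | 12 to 24 (+12) | 50 − 10×12/8 = 35.0 | 32.9 |

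For r from 0.3 to 0.7 the raw gain runs from 7.2 to 25.2 points. In no case under these two assumptions does S rise. With σ = 0.25μ + 2 the largest fall is 33.2 to 26.0 (r = 0.3, entry at 3 months) and the smallest is 41.0 to 39.7 (r = 0.7, entry at 6 months).

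**2. What it does to the comparison between arms.** At a common T2 age, S = a + b × raw with b = 10/σ in both arms. The adjusted group difference and its standard error are both multiplied by b, so the test statistic is unchanged. A rank test is unaffected by any strictly increasing transformation. The normed baseline covariate is measured before the intervention begins, so using it does not favour either arm.

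**3. What a floor would do, if there is one.** Assume true standing is normal with SD 1, arms are 0.5 SD apart, and scores below a floor c are recorded as c. With m the arm mean and k = c − m, the recorded mean is cΦ(k) + m(1 − Φ(k)) + φ(k). Divide the recorded difference by the pooled SD of the floored scores, because the floor shrinks the SD too.

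| Floor | Control mean | Controls at floor | Recorded difference | Pooled SD | Standardised effect |
|---|---|---|---|---|---|
| −3 | −2 | 16% | 0.45 | 0.905 | 0.49 |
| −3 | −2.5 | 31% | 0.39 | 0.808 | 0.48 |
| −3 | −3 | 50% | 0.30 | 0.669 | 0.45 |
| −4 | −2 | 2% | 0.49 | 0.987 | 0.50 |
| −4 | −2.5 | 7% | 0.48 | 0.961 | 0.50 |
| −4 | −3 | 16% | 0.45 | 0.905 | 0.49 |

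The difference alone falls by up to 40%. The standardised effect, which drives sample size, falls by about 1–11% with the floor at −3 SD and by under 2% at −4 SD.

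A simulation of the baseline-adjusted ANCOVA gives the cost in power. It assumes 12 completers per arm (16 × 0.75), an effect of 1 SD, a baseline correlation of 0.5 and two-sided 0.05. Power is about 0.75 without a floor, 0.72 with 30% of the control distribution at the floor, 0.64 with 50% and 0.54 with 70%. Type I error with a floor stayed at about 0.03–0.05.

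**The case against.** The strongest reply is that the planned efficacy test does not analyse change. It compares arms at 12 months corrected age with baseline adjustment. Better function in the VISIBLE arm at that age would give higher normed scores, and any flat or falling trajectory produced by the norms would be common to both arms. This stands, and it limits the point to within-child and within-group change.

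Three further replies carry weight in part.

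- The article calls the test responsive in this population. It does not say for which score, so this does not rescue the normed one.
- The text never says that the norms are age-specific, and a 0–100 range leaves the score type open. Age-specific norms are the natural reading of a norm-referenced developmental instrument, and the uncertainty is itself a reason to name the score.
- Norming adjusts for age, whereas a raw score mixes function with age. That is true with entry spread over 3–6 months, and it is why the fix needs age in the model.

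A reader might also extend the point to the PDMS-2, which the article says "is a standardised and normed scale for children aged from birth to 6 years and has been validated for use as a discriminative measure". The article does not say which PDMS-2 score will be analysed, nor that a normed PDMS-2 score measures change, so the extension is not supported.

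**Conclusion.** The point holds in a limited form. The PEDI-CAT sentence gives a norm-referenced score the task of measuring change over a period when the norms move, and such a score can miss or reverse a real gain within a child or a group. This rests on reading the norms as age-specific. The direction follows from the algebra, but the sizes shown depend on assumed norms.

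Two stronger readings are tempting and are not supported. One is that a VISIBLE effect would be hidden or reversed: the comparison between arms at a common age is not biased by norming. The other is that these infants will cluster at the floor of the scale: the article gives no floor and no distribution, and the acuity entry criterion does not concern PEDI-CAT function. If a floor were reached, the cost would be some sensitivity, modest in the 0.5 SD illustration and larger only if well over half of the infants sat there.

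The weight is minor: one secondary outcome in a pilot.

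**What to change.** Name a PEDI-CAT score not referenced to age, either the raw score or an item-scaled ability score, for describing change from T1 to T2 and for the T2 comparison between arms. Include corrected age at assessment in the model. Keep the normative score to describe standing against the reference group, and remove from the conversion sentence the clause that gives it the job of measuring change.

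The cost is one sentence in the protocol. Raw scores already exist, since they are what is converted. The downsides are one extra covariate with 16 infants per arm (about 12 after 25% withdrawal) and a score less familiar to readers, who can still be shown the normed values in a table. The change does not guarantee freedom from floor effects, so the share of infants at the lowest score should be reported whichever score is used.

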### Data analysis plan

A multisite RedCap programme database will be used for this study. Study personnel at each site will enter the data onto RedCap, a secure web platform for the construction and management of surveys and online databases. All the data of the same patient will be collected under an ID number. Videos of sessions will be taken to ensure fidelity of intervention visits provided by the study therapists.

All measures will be undertaken to avoid missing data for the primary outcome. Rescheduling of appointments for assessments will be done if the data collection cannot be completed in one appointment. Should vital data be missing, use of all available data will be used, as recommended through methods such as multiple imputation and likelihood-based analysis.

Statistical analysis will be conducted using SPSS following standard methods for RCTs. Intention-to-treat analysis will be applied to minimise inflation of treatment effects, consistent with Consolidated Standards of Reporting Trials (CONSORT) guidelines.^46^ Descriptive statistics will be used to summarise baseline characteristics and outcome measures for both treatment groups, with continuous variables reported as means and SDs (if normally distributed) or medians and IQRs (if skewed), and categorical variables as frequencies and percentages. Normality of continuous data will be assessed using the Shapiro-Wilk test and visual inspection of histograms and quantile-quantile (Q-Q) plots. If data are normally distributed, intervention efficacy will be tested using general linear models, specifically Analysis of Covariance (ANCOVA), adjusting for baseline values. If substantial skewness is observed and not resolved through transformation, non-parametric alternatives such as the Mann-Whitney U test for between-group comparisons will be used. Appropriate adjustments for multiple comparisons will be applied where necessary.

Brain MRI analysis will include classification and semi-quantitative assessment of brain structure by a paediatric neurologist masked to clinical history. In term-born infants, structural MIRs (sMRIs) will be classified according to the Hammersmith Term Hypoxic Ischaemic Encephalopathy (HIE) patterns.^47 48^ Basal ganglia and thalamic (BGT) lesions will be classified as: (i) mild, focal subtle abnormalities with normal appearance of the posterior limb of the internal capsule (PLIC); (ii) moderate, multifocal lesion with equivocal or abnormal signal intensity within the PLIC; (iii) severe, widespread abnormalities involving all BGT structures and PLIC.^49 50^ White matter (WM) changes are classified as: (1) mild, periventricular WM changes difficult to differentiate from normal appearances and therefore not classified as abnormal; (2) moderate, small focal lesions without loss of grey matter/WM differentiation; and (3) severe, larger areas of abnormality with loss of grey matter/WM differentiation, consistent with infarction.^51^

MRI pattern will be described as: (1) pattern 1: BGT lesions with severe WM abnormalities; (2) pattern 2: BGT lesions with mild or moderate WM abnormalities; (3) pattern 3: only thalamic lesions; (4) moderate WM lesions and (5) normal or mild WM changes in an infant aged 5 days.^52^ This semi-quantitative scoring system is used to assess the hemispheres, subcortical structures, corpus callosum and cerebellum with particular attention to the visual pathways. In children aged >12 months CA with early brain injury, the structural MRIs will be assessed using the qualitative measure of the extent of brain lesion based on the Fiori scale.^53^ The extended version of the deep grey matter area will be applied^54^ (the detailed involvement of the thalamic nuclei and globus pallidus and/or putamen will be assessed). For sMRI, the three orthogonal T2-weighted images (T2W) will be combined into a single high-resolution T2W MRI using image super-resolution.^55^ This allows the high-resolution T2W images to be segmented into tissue types and regions of interest using the developing Human Connectome Project (dHCP) structural pipeline, as^56^ well as generate measures of the cortical surface using a manually annotated neonatal atlas.^57 58^ Region-of-interest and voxel-based analysis will be calculated and their association with vision and motor skills will be investigated.

Where diffusion MRI (dMRI) is available, the analysis would provide quantitative information regarding the white matter microstructure using the fractional anisotropy (FA), fibre density and fibre orientation (tractography). Fractional anisotropy and mean diffusivity (MD) will be estimated using maps of diffusion tensor imaging (DTI) metrics and intracellular volume fraction, isotropic volume fraction and orientation dispersion would be calculated using NODDI metrics. Cortical and subcortical areas of interest will be demarcated using the age-appropriate atlases and the summary of DTI measures will be calculated. Estimation of fibre orientation distribution (FOD) and fibre densities of young-appearing and older-appearing white matter will be done using multi-shell multi-tissue constrained spherical deconvolution for neonates in MRtrix.^59 60^ Whole-brain voxel-based analysis of FA and MD would be performed using tract-based spatial statistics.^61^

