### Randomisation

Based on clinical data, we estimate to recruit 6–7 participants per site in an 18-month period. We aim to recruit a total of 32 participants, 16 per group (block randomisation), consistent with the number of participants suggested for an exploratory pilot RCT,^27^ increased to allow for participants’ withdrawal rate of up to 25%.

Randomisation into one of two groups will be completed through an independent automated process via a concealed allocation through the Research Electronic Data Capture (RedCap),^28^ a secure, web-based application designed to support research data capture. All sites have access to RedCap and will use the same randomisation module (central randomisation). Randomisation sequence was generated by an independent statistician not involved in the trial and without knowledge of the trial details. The sequence was imbedded into RedCap by a team member not involved in recruitment, screening or treatment of participants. Outcome assessors and data analysts will be masked to the group allocation of the individual participants.

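### If transformation does not cure skewness, the only named fallback is the Mann-Whitney test, which drops the baseline that the ANCOVA route uses

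*Protocol article*

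**What the plan says.** The Data analysis plan sets two routes.

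- **Normal data:** general linear models, "specifically Analysis of Covariance (ANCOVA), adjusting for baseline values".
- **Skewed data:** "If substantial skewness is observed and not resolved through transformation", then "non-parametric alternatives such as the Mann-Whitney U test for between-group comparisons will be used".

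The choice rests on this check: "Normality of continuous data will be assessed using the Shapiro-Wilk test and visual inspection of histograms", together with Q-Q plots. No baseline term appears on the second route.

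The section Primary outcome measure has vision assessed at T0 and again at T2, so a baseline exists for the primary outcome. One of the vision measures is the near detection scale, "a 10-point scale ranging from no light awareness (0) to 0.1 cm".

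On size, the section Randomisation states: "We aim to recruit a total of 32 participants, 16 per group (block randomisation"), "consistent with the number of participants suggested for an exploratory pilot RCT", with an allowance for a "withdrawal rate of up to 25"% loss. The article states no effect size, SD, significance level, baseline-outcome correlation or power.

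**The concern.** The plan values the baseline on one route and leaves it out on the other, although the same infants supply it in both cases. Three things follow.

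- **Precision.** With 24 to 32 infants, baseline adjustment is one of the few free sources of precision.
- **Quantity estimated.** A check made on the trial data decides whether an outcome is reported as an adjusted mean difference or as an unadjusted rank comparison, so the quantity can change from outcome to outcome. The Background says that, if there is initial evidence of efficacy, the data will be used to design a powered trial. A Mann-Whitney p-value gives that trial no baseline-adjusted effect in score units.
- **Trigger.** ANCOVA needs roughly normal residuals. An outcome can look skewed because the baseline is skewed while the residuals are acceptable, and the reverse can also happen. Testing the data can send an outcome down the wrong route.

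**Working it through.** **Inputs from the article.** 16 per group and up to 25% withdrawal: 16 × (1 − 0.25) = 12 per group if all the allowed losses occur. In reverse, 12 / 0.75 = 16 and 24 / 0.75 = 32. The starting 12 is inferred; the article does not state it. There is no power figure to reproduce.

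**Assumed inputs.** Two-sided alpha 0.05; shift d = 0.8 SD on the latent scale; baseline-outcome correlation ρ from 0.3 to 0.7.

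**Step 1: what the baseline is worth with normal data.** ANCOVA multiplies the residual variance by 1 − ρ². Dropping the baseline is then like needing 1/(1 − ρ²) times the infants: 1/0.91 = 1.10, 1/0.75 = 1.33 and 1/0.51 = 1.96 at ρ = 0.3, 0.5 and 0.7.

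Approximate power is Φ(d / √(2(1 − ρ²)/n) − 1.96). For Mann-Whitney, replace n by 3n/π and set ρ = 0. At n = 12 and d = 0.8:

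- ANCOVA, ρ = 0.5: 0.8 / √(2 × 0.75/12) = 2.263, power 62%.
- ANCOVA, ρ = 0.3 and 0.7: 54% and 78%.
- Mann-Whitney: 3n/π = 11.46; 0.8 / √(2/11.46) = 1.915, power 48%.

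The gap is 6, 14 and 30 points. This is the case in which the plan would *not* switch, so it shows only the value of the baseline, not the cost of the rule.

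**Step 2: once the fallback is used.** Simulated power (2,500 trials per cell, Monte Carlo standard error at most √(0.25/2500) = 1 point), Mann-Whitney against rank ANCOVA, d = 0.8:

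| Data | n per arm | ρ = 0.3 | ρ = 0.5 | ρ = 0.7 |
|---|---|---|---|---|
| Floored ordinal | 12 | 40 v 43 | 40 v 48 | 40 v 57 |
| Floored ordinal | 16 | 51 v 55 | 52 v 60 | 53 v 71 |
| Log-normal, multiplicative effect | 12 | 44 v 47 | 44 v 54 | 44 v 68 |
| Log-normal, multiplicative effect | 16 | 55 v 59 | 56 v 67 | 56 v 81 |

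The difference is about 3 to 25 points and grows with ρ. The top of the range comes from the log-normal rows. A separate simulation of a floored 10-point scale at 12 per arm gave 42 v 46, 41 v 51, 41 v 55 and 42 v 63 at ρ = 0.3, 0.5, 0.6 and 0.7. With log-normal data and an additive shift, Mann-Whitney already has 87-96% power, and the gain is only about 1 to 8 points. With no effect (ρ = 0.5), rank ANCOVA rejected in 4.3-5.3% of the skewed and ordinal runs.

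**Step 3: the whole rule.** The plan tries a transformation before it switches. A further simulation included that step, with Shapiro-Wilk rejection in either arm standing in for the plan's mixed test-and-plot judgement.

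- **Log-normal, ρ = 0.6:** the plan's rule had 61% power against 59% for rank ANCOVA at 12 per arm, and 75% against 72% at 16. Over ρ = 0.3-0.7, the fallback was reached in only about 8-10% of trials. There was no loss.
- **Floored 10-point scale:** 44 v 45 at ρ = 0.3 and 49 v 55 at ρ = 0.6 with 12 per arm; a loss of 11 points at ρ = 0.6 with 16 per arm. Over ρ = 0.3-0.7 and 12-16 per arm, the loss was about 0 to 12 points.

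**The case against.** The best defence has five parts.

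1. **Mann-Whitney is only an example.** The words *such as* leave other methods open, and an SAP may name one. This is true, so the plan does not forbid an adjusted rank test. But the only test it names has no baseline term, and leaving the choice open until the data are seen is no better.
2. **The switch comes late.** It needs substantial skewness that survives transformation, judged by plots as well as a test. This stands, and it removes the loss for data that a log transform cures. Acuity, on a range of 0.23 to 26 cycles/cm (about 113-fold), is an obvious candidate for logs.
3. **Under skew, Mann-Whitney can beat ANCOVA on raw scores.** With a multiplicative log-normal effect, 12 per arm and ρ = 0.5, it had 44% power against 36%. This stands: leaving raw ANCOVA may be right. The fault is in leaving the baseline behind as well.
4. **Skewed outcomes still get medians and IQRs by group.** True, but these are unadjusted summaries, not an adjusted treatment effect.
5. **This is a pilot, with feasibility and acceptability as its main objective and no power target.** True. No stated figure is contradicted, which limits the weight of the point. Preliminary efficacy is nevertheless a stated aim, and the repair needs no data.

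**Conclusion.** The point holds in a limited form. The named fallback drops a baseline that has been measured and changes the quantity estimated, and the normality check is applied to the data and not to the residuals. On the assumptions above, the cost is roughly 3-25 points of power once the fallback is used. For the whole rule it is about 0-12 points on a floored scale and nil for log-normal data. The correlation, the effect size, the alpha and the presence of a floor are all assumptions.

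A reader might infer more than the documents support:

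- **A general loss of about 15 points.** That figure compares always using Mann-Whitney with rank ANCOVA near ρ = 0.6 and ignores the transformation step.
- **Mann-Whitney as the usual route for the vision outcomes.** The article reports no score distributions. A floor on the 0-9 scale is plausible in infants selected for low acuity, but it is not stated.
- **Nystagmus and strabismus as examples.** As categorical signs, they fall outside a rule written for continuous data.
- **Baseline adjustment for every outcome.** BSID-III is measured only at T2.

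**What to change.** In the Data analysis plan, for every outcome with a baseline measurement:

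1. Judge normality on the ANCOVA residuals.
2. If transformation fails, replace Mann-Whitney with a baseline-adjusted rank analysis (Quade rank ANCOVA) or, for ordinal scales, a proportional-odds model with the baseline score. Name in advance which applies to which outcome; with 24 to 32 infants spread over up to ten levels, some categories may be sparse.
3. On either route, report the baseline-adjusted difference in score units with a 95% CI, for example by bootstrap, so that the estimate keeps the same meaning across outcomes and can inform the next trial.
4. State that outcomes measured only at T2 (BSID-III) are compared without their own baseline.

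The cost is a few sentences in the plan and a few lines of analysis code. It needs no extra visits, data or infants.
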